|----------------------------------------------------------------------------------------------------------------------------|-------------------------------------------------------------------------------------------------------------------------------------------|----------------------------------------------------------------------------------------------------------------------------------------------------------------------------------------------------------------------------------------------------------------------------------------------------------------------------------------------------------------------------------------|
| B25                                                                                                                        | In the past 12 months have you...                                                                                                         | 
Yes    No
 
A. Sold sex for money?    1    2
 
B. Sold sex for goods or favours?    1    2
 
C. Injected drugs without a prescription?    1    2
 
MEN ONLY: Had sex with another man?    1    2
 |
| B26                                                                                                                        | INTERVIEWER OPINION:
HOW KNOWLEDGEABLE IS THIS
RESPONDENT LIKELY TO BE ABOUT
THE ACTIVITIES AND PATRONS AT THE
SITE OR EVENT? | 
Extremely knowledgeable    1
 
Knowledgeable    2
 
Not very knowledgeable    3
                                                                                                                                                                                          |
| IF RESPONDENT ANSWERED "NO" TO ALL QUESTIONS IN B25, THANK THE RESPONDENT FOR PARTICIPATING
AND END THE SURVEY. |                                                                                                                                           |                                                                                                                                                                                                                                                                                                                                                                                        |
| B27                                                                                                                        | IF RESPONDENT ANSWERED "YES" TO
ANY QUESTION IN B25 CONTINUE TO
PART III OF SURVEY.                                                 | SHOULD YOU COMPLETE PART III?: 
Yes    No
 
1    2
                                                                                                                                                                                                                                                            |
| B28                                                                                                                        | IF RESPONDENT ANSWERED "YES" TO
ANY QUESTION IN B22 BUT DID NOT
COMPLETE PART III, PLEASE EXPLAIN
WHY.                           | EXPLAIN:                                                                                                                                                                                                                                                                                                                                                                               |

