### C. Population Size Estimate Analysis

#### Population Size Estimation Analysis using PLACE

1. For each area that was mapped, we will estimate the number of sites in each area by type of site and type of key population at site
2. We will estimate the number of each type of key population at each type of site
3. We will provide a map of sites indicating the number of key populations at each
4. We will estimate the total number of key population member in each zone and in the sub-national areas included in the estimate
5. We will extrapolate the estimate to include areas not covered
6. We will estimate the number of key populations missing from the estimate based on findings from formative research
7. We will refine the size estimates based on mobility of key populations, visits to multiple venues, and variety in frequency of attendance
8. We will use the size estimates to calculate coverage for components of the comprehensive program for key populations

The following steps for size estimation will be followed:

1. Review data to confirm completeness of site lists and adequacy of estimates of the number of key population members at each site. Check the quality of the data by comparing the number of sites named and the number of times each was named with the number of reports naming a site from community informants. Check that there are sites named in every area included in the mapping activity. Confirm that the interviewers included members of each key population and that targets for type and number of community informants were reached. Review the list of sites that were not located and re-visit a random sample to confirm that the sites do not exist.
2. Calculate a point estimate for the number of each key population at each site based on the reported range provided. At each site, informants will be asked to estimate the maximum and minimum number of key populations at the site at a busy time.
3. Separate the estimates from sites that were initially identified as sites with key populations from sites that were not reported to have key populations. The rationale for treating the two types of sites differently is that they are sampled with different sampling fractions and the expected number of key populations at the sites reported to have key populations will be higher than at the other sites.
4. Add up the median number of key populations at each site for an initial crude estimate of the size of each population.

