5. Produce a map illustrating number of key populations at each site using the median for the size estimate.
6. Adjust estimates based on information about frequency of visiting sites, frequency of visiting more than one site in a day, and the percentage of sites that have key populations but were not initially identified as sites with key populations.
7. Use the formula below to estimate the size based on the key population sites and separately for the other sites. The formula is:

$$E_i = s_i(1-p_i) + (s_i * p_i / m_i)$$

$E_i$  = the estimated key population members in an area

$s_i$  = estimate at the site level

$p_i$  = Proportion of female sex workers solicit in two or more sites

$m_i$  = Mean number of places a female sex worker solicit

For example,

If  $s_i$  from all the key population sites is 10,000 and 10% solicit in other sites, and the mean number of places the 10% solicit is 2 then the estimate is

$$10,000 (1 - 0.1) + (10,000 * 0.1 / 2)$$

$$= 9000 + 10,000 * 0.05$$

$$= 9000 + 500$$

$$= 9500$$

The formula is reasonable because it counts all of who are only at one place and for the ones who go to more places, the percentage of that group is reduced because the people might have counted at more than one place. This could be repeated for key populations at Other Sites. If 500 were found at Other Sites, the estimate would be 10,000.

8. Use the area estimates to develop national estimates. National estimates are developed by extrapolation of data. One approach is to estimate the percentage of the male and female population who is a member of a key population in the areas where the mapping and size estimation activity was done. Apply the percentage estimated in one area to the areas that are similar.
9. Meet with stakeholders to review the estimates and ensure that the size estimates are reasonable and acceptable to the stakeholders.
10. The size estimates can be used as the denominator in coverage estimates. If the randomly selected members of the key population were asked questions about access to testing and other prevention initiatives, additional analysis of their responses would be useful.

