| 
B5
                                                                | 
How many women work at this site over the course of a busy day and night? That is they are employed by the site or they are self-employed and work here.
                                                                                                                       | 
NUMBER:
 
_____
                                                                                                                                                                                                                                                                                                                                                                                                                                                                                                                                                                                                                                                                                                                                                                                                                                                                                                                                                                                                                                                                                                            |            |     |    |            |                                       |   |   |   |                                                    |   |   |   |                                                  |   |   |   |                                               |   |   |   |                                                 |   |   |   |                             |   |   |   |                                     |   |   |   |                                        |   |   |   |                                       |   |   |   |                                                                          |   |   |   |

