| 
B6
 
A-B
 | 
Some women exchange sex for money and some exchange sex for goods or favors. Goods or favors includes housing, transportation, food or gifts.
 
A. Of the (NUMBER FROM B5) women who work here, how many do you estimate occasionally or regularly exchange sex for money?
 
B. Of the (NUMBER FROM B5) women who work here, how many do you estimate exchange sex for goods or favors?
 |                                                                                                                                                                                                                                                                                                                                                                                                                                                                                                                                                                                          | 
A. NUMBER: _____
 
B. NUMBER: _____
 |   |   |      |   |       |   |       |   |       |   |         |   |         |   |         |   |         |   |         |    |         |    |           |    |           |    |

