| 
B7
            | 
On a busy day, how many women aged 18 and older come here as patrons (to socialize, drink alcohol, etc.) over the course of the entire day and night?
 
READ OPTIONS. CIRCLE ONE CODE BETWEEN 0 AND 13 THAT INDICATES THE CORRECT RANGE.
                                                                                                                                                                                 | 
CIRCLE ONE CODE BETWEEN 1 AND 13:
 
 
 0	1	
 
 1-14	2	
 
 15-29	3	
 
 30-49	4	
 
 50-99	5	
 
 100-149	6	
 
 150-199	7	
 
 200-299	8	
 
 300-399	9	
 
 400-499	10	
 
 500-999	11	
 
 1000-1999	12	
 
 Over 2000	13	
 
 |                                                               | 0 | 1 | 1-14 | 2 | 15-29 | 3 | 30-49 | 4 | 50-99 | 5 | 100-149 | 6 | 150-199 | 7 | 200-299 | 8 | 300-399 | 9 | 400-499 | 10 | 500-999 | 11 | 1000-1999 | 12 | Over 2000 | 13 |

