| 
B9
            | 
On a busy night, how many of the _____(NUMBER FROM B8) female patrons who come here do you think exchange sex for money? IF NONE, ENTER 0.
                                                                                                                                                                                                                                                                                    |                                                                                                                                                                                                                                                                                                                                                                                                                                                                                                                                                                                          | 
NUMBER: _____
                                   |   |   |      |   |       |   |       |   |       |   |         |   |         |   |         |   |         |   |         |    |         |    |           |    |           |    |

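### Form B lets one woman be counted as a sex worker both among site workers and among patrons, so adding B6A and B9 can inflate the PLACE size estimate by an unknown factor

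*Protocol*

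**What the plan says.** Form B (Protocol, Appendix 3, Part II) collects female sex worker numbers through two routes.

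- **Workers.** B5 asks for the number of women who work at the site over a busy day and night, explained as "they are employed by the site or they are self-employed and work here". B6A then asks, of the "women who work here, how many do you estimate occasionally or regularly exchange sex for money".
- **Patrons.** B7 asks "how many women aged 18 and older come here as patrons (to socialize, drink alcohol, etc.) over the course of the entire day and night", B8 turns that range into a best guess, and B9 asks how many of those "female patrons who come here do you think exchange sex for money? IF NONE, ENTER 0".

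The analysis is in Protocol VIII.C, in the numbered steps for size estimation using PLACE. Step 2 needs one point estimate per key population per site and says that "informants will be asked to estimate the maximum and minimum number of key populations at the site at a busy time". Step 4 is to "Add up the median number of key populations at each site for an initial crude estimate of the size of each population". Step 6 is to "Adjust estimates based on information about frequency of visiting sites, frequency of visiting more than one site in a day", and also to allow for sites with key populations that were not identified as such at first. Step 7 applies E = s(1 − p) + s·p/m, where p is the proportion of female sex workers soliciting at two or more sites and m is the mean number of places.

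**The concern.** B5 explicitly includes self-employed women. A freelance sex worker who looks for clients in a bar fits that description, and she also fits a description of a woman who comes there as a patron. No instruction in B7 to B10 removes women already given in B5 and B6, so the two counts are not mutually exclusive.

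The form avoids this for men: B11 asks for one total of men, and B13 and B14 take subsets of it. Only women are split into two groups that are never reconciled.

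The size estimate is meant to serve as a denominator for programme coverage (Protocol VIII.C, step 10, and Table 4). A denominator that is too large makes coverage look lower than it is. The fault lies in the data-collection form, so an analysis plan cannot fully repair it: once B6A and B9 are recorded as two totals, the overlap can be bounded but not recovered.

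**Working it through.** **Inputs from the protocol.** The step 7 worked example has "from all the key population sites is 10,000 and 10% solicit in other sites", with a mean of 2 places for that 10%. So s = 10,000, p = 0.10 and m = 2.

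**Reproducing the protocol's figure.** E = 10,000 × 0.9 + 10,000 × 0.1 / 2 = 9,000 + 500 = 9,500, as stated. Adding the example's 500 from Other Sites gives 10,000, also as stated.

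**Does step 7 remove a within-site duplicate?** Rewrite the formula as E = s × [(1 − p) + p/m] = s × 0.95 in the example. E is proportional to s. The terms p and m describe women who solicit at several sites and say nothing about one woman entered twice at the same site. Any within-site duplication in s therefore passes into E in full.

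**Overlap model (assumed).** Let T be the number of distinct women and o the share of them who appear in both B6A and B9. If the site count is B6A + B9, then s = T(1 + o), and the inflation factor is 1 + o. The documents give no value for o, so the whole range from 0 to 100% is shown. Purely as an illustration, suppose that the example's s = 10,000 had been formed by adding the two items:

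| o | T = 10,000 / (1 + o) | E on distinct women | 9,500 / E |
|---|---|---|---|
| 0% | 10,000 | 9,500 | 1.00 |
| 5% | 9,524 | 9,048 | 1.05 |
| 10% | 9,091 | 8,636 | 1.10 |
| 20% | 8,333 | 7,917 | 1.20 |
| 50% | 6,667 | 6,333 | 1.50 |
| 100% | 5,000 | 4,750 | 2.00 |

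**At one site.** With B6A = 10, B9 = 10 and 5 women in both, the form records 20 against 20 − 5 = 15 distinct women, a factor of 20/15 = 1.33.

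**What completed forms can still tell.** The number of distinct women is B6A + B9 minus the overlap, and the overlap lies between 0 and the smaller of the two counts. Taking the informant's counts as given, the distinct number therefore lies between max(B6A, B9) and B6A + B9. In the example that is 10 to 20.

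**The case against.** A reader might infer that the site counts are inflated and the estimate is biased upward. The documents do not go that far, for these reasons.

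- **No combining rule is stated.** Steps 2 to 7 never mention B6A or B9 and never say that they are added. Step 2 speaks of a minimum and a maximum, which Form B does not collect for sex workers. The rule may sit in an analysis plan that is not at hand. This stands, and the inflation is therefore conditional on adding the items.
- **Worker and patron read as separate roles.** B7 describes patrons as people who come to socialise or drink. Protocol VI.C, Step 4, samples patrons and workers separately. The worker question comes first in the same interview, so some informants will place freelancers under B5 and leave them out of B7. This also stands: o may be zero at some or all sites.
- **Other features affect the net direction.** B7 to B9 cover women aged 18 and older, while the study population starts at 15, and the plan adds a correction for members missed. Possible double counting is one upward component, not a proven net bias.
- **A pilot and pre-test are planned** (Protocol VI.C, Step 1, and VII.E) and could catch unclear wording. Neither mentions this overlap.

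The objection does not remove the gap itself: the items are not made exclusive, and no later step deals with a woman counted twice at one site.

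**Conclusion.** The point holds as a conditional one. Form B permits the same woman to be counted in B6A and B9, and the protocol neither excludes the overlap nor says how the two items form the site count. If they are added, the female sex worker estimate is multiplied by 1 + o, between 1.00 and 2.00 over the full assumed range. The upper end needs every sex worker at a site to be counted in both items. There is no inflation if informants keep the groups apart, or if only one item is used. Using one item alone would instead leave out either the women who work there or the patrons.

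Two further inferences are tempting but unsupported. The 5% reduction in the step 7 example is hypothetical, so it is no yardstick for the size of this effect. Nor do the documents show that overlap is greater at particular venue types or that it distorts comparisons between areas, although either is possible.

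**What to change.** 1. **Form B.** Put the exclusion at B7 and carry it through B8, B9 and B10, for example: *Please leave out the women you have just counted in B5 as working here; how many other women aged 18 or over come as patrons?* It has to begin at B7, because the interviewer must probe whenever B8 falls outside the B7 range. An exclusion that started at B8 could make correct answers fail that check.
2. **Protocol VIII.C, step 2.** State that the site count of women selling sex for money is B6A + B9 under that wording, and reconcile this with the minimum and maximum that the step now describes.
3. **Forms already completed.** Carry max(B6A, B9) and B6A + B9 through the estimation as lower and upper bounds for each site, and report both totals.

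The cost is one sentence on the form, repeated briefly in the follow-up items, and one definition in the analysis section. No extra interviews are needed.

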**APPENDIX 4. Form C Patron and Worker Interview Questionnaire**

**FORM C: Patron and Worker Study Interview**

| PART I – COMPLETE BEFORE INTERVIEW |                                                                                |                                                                                                                                                                                      |
|------------------------------------|--------------------------------------------------------------------------------|--------------------------------------------------------------------------------------------------------------------------------------------------------------------------------------|
| NO.                                | QUESTION                                                                       | RESPONSE                                                                                                                                                                             |
| Q1                                 | Date:                                                                          | Day   Month   Year                                           |
| Q2                                 | Interviewer Code:                                                              | Interviewer Code:                                                                                                                            |
| Q3                                 | Type of social mobilizer present:                                              | No social mobilizer present during site visit 0
Sex worker 1
MSM 2
Trans woman (Male to female) 3
Trans man: (Female to male) 4
Person who injects drugs 5
Other 6 |
| Q4
A-C                          | Geographic Code of Site:                                                       | A. Province   B. District   C. Zone                          |
| Q5                                 | Site ID Number:                                                                | Site Number: _____                                                                                                                                                                   |
|                                    | Site Name Given by Community Informant:
IF WEBSITE, INDICATE EXACT WEBSITE. |                                                                                                                                                                                      |
| Q6A                                | C. Verified Site Name:                                                         |                                                                                                                                                                                      |
|                                    | Site Address Given by Community Informant:                                     |                                                                                                                                                                                      |
| Q6B                                | D. Verified Site Address:                                                      |                                                                                                                                                                                      |
|                                    | Landmark Given by Community Informant:                                         |                                                                                                                                                                                      |
| Q6C                                | C. Correct Landmark:                                                           |                                                                                                                                                                                      |

|           |                                                                                                                                                                       |                                                                                                                                                                                                       |
|-----------|-----------------------------------------------------------------------------------------------------------------------------------------------------------------------|-------------------------------------------------------------------------------------------------------------------------------------------------------------------------------------------------------|
| Q7
A-C | Was the site found?                                                                                                                                                   | A. Location not found 0
Location found, interview conducted 1
Location closed 2
Location found, informant declined 3
Not a duplicate location, but other 4
Duplicate location 5 |
|           | IF "OTHER" IS SELECTED FOR PART A, EXPLAIN.                                                                                                                           |                                                                                                                                                                                                       |
|           | IF SITE IS A DUPLICATE LOCATION (FOR EXAMPLE SITE WAS ALREADY VERIFIED UNDER A DIFFERENT NAME), WRITE THE NUMBER FOR THE OTHER SITE THAT THIS SITE DUPLICATES IN Q7C. |                                                                                                                                                                                                       |
|           |                                                                                                                                                                       | B. IF OTHER (Q7A = 4), EXPLAIN: _____
C. IF DUPLICATE (Q7A = 5), OTHER SITE NUMBER: _____                                                                                            |

| PART I – CONTINUED |                                                                                                                                                                                                |                                                                                                                                                                                                       |                                                                                                                                                                                                                    |  |  |
|--------------------|------------------------------------------------------------------------------------------------------------------------------------------------------------------------------------------------|-------------------------------------------------------------------------------------------------------------------------------------------------------------------------------------------------------|--------------------------------------------------------------------------------------------------------------------------------------------------------------------------------------------------------------------|--|--|
| NO.                | QUESTION                                                                                                                                                                                       |                                                                                                                                                                                                       | RESPONSE                                                                                                                                                                                                           |  |  |
| Q8
A-B          | GPS Coordinates:
USE THE GPS UNIT. WRITE COORDINATES HERE.
FOR LONGITUDE: ALSO INDICATE WHETHER WEST OR EAST.
FOR LATITUDE: ALSO INDICATE WHETHER NORTH OR SOUTH.                     |                                                                                                                                                                                                       | A. Longitude: _____
B. Latitude: _____                                                                                                                                                            |  |  |
| Q9A                | Type of Site (USE CODES BELOW)
CODES 1 -22 ARE FOR TYPES OF VENUES.
CODES 23-25 ARE FOR EVENTS. IF A WEBSITE, CIRCLE 26.                                                                 |                                                                                                                                                                                                       | ENTER 1 CODE:
A. 
 
 		
 
 |  |  |
|                    |                                                                                                                                                                                                |                                                                                                                                                                                                       |                                                                                                                                                                                                                    |  |  |
|                    | Formal bar 1
Informal bar 2
Night/Exotic club 3
Massage parlor 4
Brothel 5
Truck stop 6
Hotel 7
Small guest house 8
Street sex worker site 9
Taxi stand/Bus stop 10 | Other street site 11
Beach/Creek 12
Park/Plaza 13
Construction site 14
Kiosk 15
Store 16
Market 17
Shopping Centre/Mall 18
Fast food/Restaurant 19
Church/Temple/Mosque 20 | Campus/School 21
Tourist attraction 22
OTHER:
Cultural event 23
Party event 24
Other event 25
Website 26
Escort service 27
Phone 28                                                 |  |  |
| Q9
B-I          | Physical characteristics of the site:
CIRCLE ONE ANSWER (1 OR 2) FOR EACH CHARACTERISTIC, A-H.                                                                                              |                                                                                                                                                                                                       | Yes No
B. Electricity available 1 2                                                                                                                                                                      |  |  |

|           |                                                                                                                                        |                                                                                                                                                                                                                                                  |
|-----------|----------------------------------------------------------------------------------------------------------------------------------------|--------------------------------------------------------------------------------------------------------------------------------------------------------------------------------------------------------------------------------------------------|
|           |                                                                                                                                        | C. Tap water available 1 2
D. Walls and ceiling 1 2
E. Inside toilet 1 2
F. Beds on site 1 2
G. Videos shown onsite 1 2
H. TV onsite 1 2
I. Bar for alcohol sales onsite 1 2  |
| Q9
J-N | Evidence of HIV/AIDS prevention activities visible at the venue:
CIRCLE ONE ANSWER (1 OR 2) FOR EACH PREVENTION ACTIVITY ITEM, A-E. | 
Yes No
 J. HIV/AIDS posters displayed 1 2
K. Condom promotion posters 1 2
L. Condoms visible 1 2
M. Lube visible 1 2
N. Sterile needles/syringes visible 1 2 |

